### Overview of the program

The intervention program will be based on Bandura theory, which states that the social environment in which people live is part of life and contributes significantly to human development, adaptation, and behavioral changes. People learn and acquire experiences observing the consequences within their environment, as well as the experiences of the people to whom they live. In this context, it is expected a behavioral change resulting from experiences.

The program comprises 2 terms: (1) teachers’ training delivered by researchers and (2) intervention delivered to pregnant women by trained teachers.

During 5 weeks, 6 teachers of Physical Education from the local center of the city hall will have 10 sessions of training (2 h each session). This training workshop, entitled “Healthy lifestyles in pregnancy,” will include the following information: (i) PA during pregnancy (session 1, 2, and 3); (ii) stages of pregnancy, cares, and recommendations (session 4); (iii) nutrition in pregnancy (session 5); (iv) motor development in the first months of life (session 6); and (v) PA strategies in daily living during pregnancy and postpartum (session 7, 8, 9, and 10). In addition, trained teachers will have a meeting once a month during the period of the intervention with the researchers to discuss and reflect about their intervention with pregnant women.

Participants allocated to the intervention group will perform a PA program, 3 times per week, one of which will be developed in the aquatic environment. Classes will last for 45/50 minutes, divided as follows warm up (7/8 min), fundamental part (30 min), and return to calm (10 min). The exercises performed are of moderate/vigorous intensity, and includes aerobic workout, strength, coordination, and flexibility. The program will include every trimester a session about nutrition developed for pregnant.

### Outcome measures

Data will be collected in 3 stages: (1) at the beginning of the program, (2) between first and third day after delivery, and (3) 1 month after delivery.

At baseline (stage 1), information about the sociodemographic profile will be collected, as well as medical history, eating and PA habits, symptoms of depression, and anthropometry. At stage 2, depressive symptoms, PA habits, childbirth information, and anthropometric data of the mother and the newborn will be gathered. At stage 3, depressive symptoms, PA, and food habits of the mother as well as anthropometric data of mother and newborn will be collected.

### Physical activity and sedentary time

PA will be gathered by questionnaire and accelerometry. Participants will use accelerometers GT1M Actigraph for 5 consecutive days (3 weekdays and 2 weekend days). The accelerometer will be attached at the right hip, with the sensor facing up, and the participants will be instructed to use it during waking hours and remove it during sleep and activities involving immersion in water, according to established procedures. In the current study, data will be collected in 2 seconds, each period of 60 minutes of consecutive zeros will be detected as nonwear time and at least 8 hours of data will be considered as a valid day.^20^ The total counts for minute will be converted to light, moderate, and vigorous activity (100–2019 counts/min for light PA, 2020–5998 counts/min for moderate PA and ≥5999 counts/min for vigorous PA) according to the cut points developed by Freedson et al.^21^ Sedentary behavior will be defined as <100 counts/min.^22^

In addition, the questionnaire “Pregnancy Physical Activity Questionnaire” validated for the Portuguese pregnant women^23^ will be used. The Pregnancy Physical Activity Questionnaire consists of 32 questions, grouped into different types of activity: household/caregiving, occupational, sports/exercise, transportation, and inactivity. Participants will estimate the time spent in each activity (none, no <30 min per day, between 30 min and 1 h per day, between 2 and 3 h per day and 3 h or more per day). The activities will be categorized by intensity as sedentary in METs (metabolic equivalent of task) (<1.5 METs), light (1.5–3.0 METs), moderate (3.1–6.0 METs), or vigorous (>6.0 METs). The duration of time spent in each activity is multiplied by its intensity to arrive at a measure of average weekly energy expenditure (MET-h week-1) attributable to each activity.^24^

### Dietary intake

Dietary intake of pregnant women in stages 1 and 3 will be obtained based on food frequency questionnaire, which has also been validated for the Portuguese population.^25^ This is a food list questionnaire in which the participants are asked to estimate the usual frequency of consumption during a specific period of time. Household measures (eg, glasses or tablespoons), food packaging, manufacturer's weight, and energy and nutritional uptake will be estimated using the software Food Processor Plus (ESHA Research Inc, Salem, OR), which includes, along with nutritional information from the United States, typical Portuguese culinary dishes, according to national information of the composition of Portuguese food table.^26^ Also, it will include raw and/or processed foods.

### Socioeconomics

The sociodemographic profile will be evaluated by a questionnaire constructed for this purpose divided into 2 sections. The first will include questions about the subject's sociodemographic characteristics (age, education level, current work status, and socioeconomic status using the Graffar index). The second section will collect general information on lifestyle habits (exercise habits of both pregnant and husband and tobacco consumption) and previous pregnancies (gestational weight gain, occurrence of gestational diabetes or hypertension, and type of birth).

### Anthropometry

We will calculate the body mass index (kg/m^2^) of the mother, through self-reported weight and height, according to the information of “pregnancy book” that all pregnant have in Portugal. Clinical information is recorded in this book, including anthropometry in all months. Through this weight data, we will calculate the body mass index in the baseline (weight before pregnancy), weight gain during pregnancy (the difference between the weight measured at the end of pregnancy and the weight before pregnancy), and the weight loss 1 month after delivery (difference between weight at the end of pregnancy and the weight 1 month after birth).

Weight, length, and cephalic perimeter of the newborn will be collected by analysis of clinical information.

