Despite all benefits described previously, it is well known that the level of PA decreases since the beginning of pregnancy,^17^ whether PA is performed at work and/or leisure.^18^ This fact is confirmed in the study of Currie et al,^19^ which indicates that the moderate and vigorous PA declined the most between the second and third trimester.

Until now, there are few intervention programs developed and implemented during pregnancy. Therefore, we will develop the intervention program “Healthy Bellies,” a partnership between University of Minho, local Hospital, and the City Hall.

The study aims to evaluate the impact of an intervention program, based on the promotion of PA, on pregnant, birth, and newborn outcomes. We hypothesize that the compliance to the intervention program is associated to a reduced (1) gestational weight gain and weight retention postpartum and (2) depressive symptoms. In addition, the intervention program will benefit the delivery (type, duration, complications) and improve infant's birth weight and length.

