## Methods

### Recruitment

In the hospital, during the first trimester biochemical screening (between the 7th and 10th week of gestation), 410 pregnant women will be invited to participate in this quasiexperimental study. Participants who want to engage in the PA program will be assigned to the intervention group after the 12th week and the others will be included in the control group, following the standard care procedures provided by health professionals in Portugal (205 women in each group).

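### Weight gain is counted from before pregnancy although the self-chosen programme starts after week 12; recording a programme-start weight and adjusting for early gain would cheaply remove the pre-programme part

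*Protocol article*

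**What the plan says.** Four statements in the protocol article bear on this point.

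- **Outcome.** The first-listed hypothesis (Introduction) is that compliance with the programme goes with "reduced (1) gestational weight gain and weight retention postpartum". Methods, Anthropometry, defines "weight gain during pregnancy (the difference between the weight measured at the end of pregnancy and the weight before pregnancy".
- **Baseline.** The same section anchors the anthropometric baseline at the same point: "we will calculate the body mass index in the baseline (weight before pregnancy".
- **Groups and timing.** Women are approached "during the first trimester biochemical screening (between the 7th and 10th week of gestation". Then: "Participants who want to engage in the PA program will be assigned to the intervention group after the 12th week". All others form the control group.
- **Data source.** Body mass index is obtained "through self-reported weight and height, according to the information of “pregnancy book” that all pregnant have in Portugal". Of that book the article says: "Clinical information is recorded in this book, including anthropometry in all months".

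Anthropometry lists three quantities to be derived from these weights: baseline BMI, gain over pregnancy, and loss one month after delivery. A weight at programme start is not among them. Statistical analysis names multivariate regression models and no covariates. Discussion acknowledges that the study is not randomised.

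**The concern.** Total gain is the sum of two parts: gain up to programme start (early gain) and gain from then to the end of pregnancy (later gain). The programme can act only on the second.

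In a randomised trial the first part would be noise with the same expectation in both groups. Here women sort themselves into groups, so nothing guarantees equal early gain. Women drawn to an exercise programme could have gained more or less in the first trimester than those who decline. In an unadjusted comparison of total gain, any such difference would be read as a programme effect, in whichever direction it happens to run. The early part also usually adds variance that the programme cannot alter.

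A baseline adjustment anchored on pre-pregnancy weight or BMI does not in itself deal with this, because that anchor also precedes the early gain.

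**Working it through.** **1. The plan's own figure.** The only sample-size calculation (Sample size) is for physical activity, not weight. With a 20% difference, 0.20 × 210.35 = 42.07 and 42.07 / 116.75 = 0.36. For two-sided 5% error and 80% power, n = 2 × (1.960 + 0.842)² / 0.36² = 121.1, so 122 per group. The stated 122 per group (244 in all) reproduces. It says nothing about precision for weight gain; below it serves only as a group size for illustration.

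**2. Bias.** Write T = E + L for total, early and later gain. The unadjusted group difference in T is the group difference in E plus the group difference in L. If the programme does nothing and later gain is equal in the two groups, what remains is the difference in E, one for one. This step needs no assumed SD.

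**3. Share of variance before the programme.** The article gives no SD for weight, so these are assumptions: SD of L 4.5 kg, SD of E 2 to 3 kg, independent. Share = SD_E² / (SD_E² + SD_L²).

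- SD_E = 2: 4 / (4 + 20.25) = 4 / 24.25 = 0.165
- SD_E = 3: 9 / (9 + 20.25) = 9 / 29.25 = 0.308

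**4. What an imbalance would do to the error rate.** Assume 122 per group, no programme effect, SD_L = 4.5 kg, SD_E = 1.5 to 3.5 kg, and E and L uncorrelated. The SD of T is then 4.74 to 5.70 kg and the standard error is SD_T × √(2/122). The chance of a significant result at nominal 5% two-sided is:

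| Assumed difference in early gain | Chance of a false positive |
|---|---|
| 0.25 kg | 6.4% to 7.0% |
| 0.5 kg | 10.5% to 13.1% |
| 1.0 kg | 27.8% to 37.8% |
| 1.5 kg | 53.8% to 69.6% |

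**5. What the extra variance would do to power.** Take the true difference that gives 80% power on later gain: 4.5 × √(2/122) × (1.960 + 0.842) = 1.61 kg. Unadjusted power on total gain is then 75.7%, 68.8% and 59.9% for SD_E = 1.5, 2.5 and 3.5 kg with no correlation. With correlations from -0.2 to 0.3 the range is 49.5% to 80.9%. The top value exceeds 80% because a small early SD with a negative correlation slightly lowers the variance of the total (ratio 0.98). Later gain adjusted for early gain gives 80.0% to 83.6% over the same grid.

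**6. Why adjustment keeps the definition.** Since T = E + L, regressing T on group, E and BMI gives exactly the same group coefficient as regressing L on group, E and BMI; only the coefficient of E changes, by 1. Total gain can stay the reported outcome while the group effect is that on gain after programme start.

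**The case against.** The strongest reply is that the quoted definition is not wrong. Gain from pre-pregnancy weight is a legitimate outcome, and the fix itself keeps it. On this view what is left is an unnamed covariate, and a condensed article may leave its covariate list to a fuller document that is not shown. Part of this stands: silence about covariates is not a decision against adjusting, and no fault is claimed on that ground. But the article does fix the outcome, the baseline anchor and the weights to be derived, and a programme-start weight is not among those. A later analysis plan can adjust for early gain only if that weight has been collected.

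Three stronger readings are tempting, and the documents do not support them.

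- **That the estimate is biased.** A reader might infer this from self-selection. Nothing in the article shows that joiners and decliners differ in early gain, and it openly says the study is not randomised. The bias is conditional.
- **That the kilogram and percentage figures describe this trial.** They rest wholly on assumed SDs, correlations and imbalances, and at one corner of the grid the variance argument reverses slightly.
- **That a measured week-12 weight would replace a self-reported one.** Anthropometry applies the self-report wording to information from that same book and does not say that the monthly weights are measured. The early-gain covariate also still uses the pre-pregnancy weight.

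It is also fair to say that weight gain does not size the study and is one of several hypothesised outcomes.

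**Conclusion.** The point holds as a cheap improvement to the analysis of the first-listed outcome, not as an error in the definition of weight gain. The structural part rests on the document alone: the outcome starts before pregnancy, the self-chosen programme starts after week 12, and any group difference in the gain between those times would enter an unadjusted effect one for one. The size is unknown. If early gain has an SD of 2 to 3 kg and later gain 4.5 kg, independent, about 16% to 31% of the variance of total gain precedes the programme.

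Adjustment deals with the pre-programme component only. Women who join may differ from decliners in later gain for reasons unrelated to the programme. The rule that a woman must complete at least 10 classes to count in the intervention group (Participants) selects further after the start. Both remain.

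**What to change.** - Keep total gain as defined in Anthropometry.
- Add one item to the abstraction from the pregnancy book: the last weight recorded at or before programme start, with its date. In controls, take the weight from the same gestational window, about week 12.
- In the weight-gain regression, include early gain (that weight minus pre-pregnancy weight) and pre-pregnancy BMI as covariates in both groups.
- State the accepted window and how missing or off-window weights are handled.
- State that the adjustment removes only the pre-programme component, and that selection into different later gain and the 10-class rule are not addressed by it.

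The cost is one more weight per woman from a book already being abstracted, and a few lines of analysis text. Some weights will be missing or fall outside the window. Random error in the recorded programme-start weight would leave a residue of any imbalance. The sample size and the outcome definition do not change.

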### Childbirth data

These data will be collected in the hospital through the analysis of the clinical information, including Apgar index, admission in neonatal care unit, neonatal morbidity, pregnancy complications (hypertensive disorders, gestational diabetes, preterm delivery, and other complications) gestation age at the delivery, labor onset (spontaneous or induced), labor duration and evolution, way of delivery, third and fourth grade perineal lacerations, epidural analgesia, and episiotomy will also be gathered in the hospital through analysis of clinical process.

### Depressive symptoms

The information related to depressive symptoms will be analyzed by the “Edinburgh Postnatal Depression Scale” questionnaire, previously used in Portugal.^27^ This questionnaire contains 10 questions, each with 4 possible answers and reports to the 7 days preceding the filling.

In Table 1 are presented the instruments used in each stages.

**Table 1 T1:**

Outcome measures

### Ethics approval and consent to participate

Before starting the program, participants will be informed about the purpose of the study and will provide a written informed consent, according to the ethical standards laid down in the Declaration of Helsinki. In addition, this study was approved by the Subcommittee on Ethics for the Life Sciences and Health of the University of Minho (id: SECVS 086/2015) on October 28, 2015 and by the Ethics Committee for Health of the Central Hospital (id: 056/2014) on December 18, 2015.

### Statistical analysis

Measures of central tendency and dispersion will be calculated for all variables of interest. Comparisons between the baseline and the endpoints of the 2 groups of the study will be performed using multivariate regression models, to address the influence of the PA program in maternal and neonatal outcomes. The data analysis will be performed using IBM SPSS, Version 23.0 (SPSS Inc, Chicago, IL), with a significance level of 0.05.

### Sample size

For sample size estimation we will use the variable of interest PA intensity in METs/h/wk. In Portugal, the PA average in pregnant is 210.35 ± 116.75 METs/h/wk.^28^ To detect 20% difference in PA between groups in the third trimester (increasing average PA in intervention group by ≈42 METs/h/wk), with type I and II errors of 5% and 20%, we will have an effect size of 0.36. A sample of 244 pregnant women (122 in each intervention and control group) is anticipated to stage 3. Assuming a dropout of 30%, we propose a sample size by stage 1 of 318 pregnant women, 159 per group; Fig. 1).

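### The 30% dropout allowance is multiplied rather than divided, so the 318 women proposed at stage 1 would give about 76% power instead of 80% if 318 is the enrolment target

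*Protocol article*

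**What the plan says.** All inputs are in the Sample size section of the protocol article. The reference value is "In Portugal, the PA average in pregnant is 210.35 ± 116.75 METs/h/wk". The aim is "To detect 20% difference in PA between groups in the third trimester", "with type I and II errors of 5% and 20" percent respectively, and the text concludes "we will have an effect size of 0.36". The number with data at the end follows: "A sample of 244 pregnant women (122 in each intervention and control group) is anticipated to stage 3". The enrolment step is the next sentence: "Assuming a dropout of 30%, we propose a sample size by stage 1 of 318 pregnant women, 159 per group".

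Two other places give a different size. The Abstract describes a study of 410 women. The Recruitment section also gives 410, as women to be invited, and in the same paragraph counts 205 in each group. Neither place derives 410 or links it to 318.

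**The concern.** The section treats 122 per group as the number needed at stage 3 and 159 per group as the number at stage 1, with 30% lost in between. These three figures cannot all hold, because losing 30% of 159 does not leave 122. The stage 1 figure looks like 122 with 30% of itself added, a common slip when a completer count is converted to an enrolment count.

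What is at stake is the stated type II error of 20%. This is the only sample size justification in the document. A team that took 318 as its target would stop 32 women short of what its own dropout assumption requires.

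**Working it through.** **Inputs (Protocol article, Sample size):** mean 210.35, SD 116.75, difference 20%, type I error 5%, type II error 20%, equal groups, dropout 30%. Sidedness is not stated; two-sided is taken because only that reproduces the plan's figure (step 2).

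**1. Effect size.** 0.20 × 210.35 = 42.07, and 42.07/116.75 = 0.360. This agrees with the plan.

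**2. Number needed at stage 3.** n per group = 2(z₀.₉₇₅ + z₀.₈₀)²/d² = 2(1.960 + 0.842)²/0.36² = 121.1, rounded up to 122. The t-test calculation gives 121.9 to 122.1, depending on whether 42.07/116.75 or 0.36 is used. The plan's 122 per group (244 in total) reproduces. A one-sided 5% test would need 2(1.645 + 0.842)²/0.36² = 95.4, or 96, which does not match.

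**3. Stage 1 size as the plan obtained it.** 122 × (1 + 0.30) = 158.6, rounded up to 159 per group and 318 in total. This is an exact match.

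**4. Stage 1 size that a 30% loss requires.** 122/(1 − 0.30) = 174.3, rounded up to 175 per group and 350 in total. The difference is 350 − 318 = 32 women.

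**5. What 318 delivers.** 159 × 0.70 = 111.3 per group (318 × 0.70 = 222.6 in total). Power = Φ(d√(n/2) − 1.960) = Φ(0.36 × √55.5 − 1.960) = Φ(0.722) = 76.5% at 111 per group; the t-test gives 76.1%. At 122 per group the same two methods give 80.3% and 80.0%. The largest loss that still leaves 122 is 1 − 122/159 = 23.3%.

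**6. What 410 would deliver, if enrolled.** 205 × 0.70 = 143.5 per group. Power = Φ(0.36 × √71.75 − 1.960) = Φ(1.089) = 86.2%, or 86.0% by t-test.

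**7. Unequal loss.** The Discussion expects more dropout in the control group. The size of the imbalance is not given, so the following is an illustration on assumed rates: 40% control and 20% intervention, still 30% overall. The equivalent equal group size is 2/(1/n₁ + 1/n₂).

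| Stage 1 per group | Left (control, intervention) | Equivalent n per group | Power (t-test) |
|---|---|---|---|
| 159 | 95.4, 127.2 | 109.0 | 75.4% |
| 175 | 105, 140 | 120.0 | 79.3% |

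On these assumed rates the imbalance costs about one further point of power in either case.

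**The case against.** The strongest objection concerns the consequence, since the arithmetic slip itself is plain. A reader might infer from the Sample size section that the trial is underpowered at 76%. The document does not support that as a flat statement. The Abstract and the count of 205 per group in Recruitment point to a study of 410. That exceeds the corrected 350 and would keep about 86% power after 30% loss. This objection stands, and it makes the 76% conditional on 318 being the enrolment target.

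The opposite inference is also tempting: that 410 already covers 350, so nothing needs to change in recruitment. That is not secure either. Recruitment presents 410 as the number of women to be invited, and 318 could then be the number expected at stage 1. The flow diagram cited in the Sample size section might connect the two figures, but it is not available here. The text alone does not settle the matter.

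Two further points carry some weight. The difference is defined for the third trimester, while the 244 is tied to stage 3, one month after delivery. Physical activity is also collected at stage 2, so if the sized comparison uses earlier data, the loss that matters could be below 30%. The document gives no loss by stage, so this remains only a possibility. Also, a uniform 30% loss is a simplification. The Discussion expects more loss among controls, and the Participants section requires at least 10 classes for a woman to count in the intervention group, which may reduce that group separately. Neither point makes 318, 30% and 244 consistent with one another.

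**Conclusion.** The stage 1 figure is wrong as written. The allowance was applied as 122 × 1.30 when the stated dropout calls for 122/0.70, so the section gives 318 where its own inputs give 350. If 318 is the enrolment target, the type II error is about 24% against the stated 20%, a loss of about 4 points of power. If 410 women are enrolled, power exceeds 80% and the defect lies only in the written rationale.

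These figures assume a two-sided 5% comparison of two means, the plan's effect size of 0.36, and 30% loss in each group between stage 1 and the analysed time point. The arithmetic is certain; which figure governs enrolment is not. Because the power loss is modest and conditional, this is a moderate correction and not a flaw that the study must resolve before it can be relied on.

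**What to change.** In the Sample size section, do one of the following:

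- replace the stage 1 figure with 350 women, 175 per group, shown as 122/0.70; or
- keep 318 (159 per group) and state that power after 30% loss is about 76%.

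In the same edit:

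- reconcile the figure with the 410 in the Abstract and Recruitment section by stating whether 410 is the number invited or the number enrolled. Changing 318 to 350 alone would leave 350 unexplained beside 410;
- state that equal 30% loss in both groups is an assumption, since the Discussion expects more loss among controls.

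The cost is a short text correction. If 410 is the enrolment figure, no further women are needed. If 318 is the enrolment target and 80% power is to be kept, 32 more women are needed at stage 1.
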